### Minimising bias

We have minimised selection bias by asking sites to approach all eligible cases and consecutive controls. All those approached but not recruited will be included in a screening log to demonstrate a non-selective approach. By minimising exclusion criteria, we aimed to design an inclusive study to support generalisation of the results.

The diagnostic criteria assessment will be undertaken by an investigator who is unaware of (blinded to) the dermatologist’s diagnosis of the participant. Investigators are trained to focus on the presence or absence of each clinical feature. The study will test a prespecified scoring algorithm proposed through the eDelphi consensus study and a prespecified diagnostic threshold decided with the expert advisory group.

Bias in the reference standard will be minimised by ensuring all participants have a confirmed diagnosis by a dermatologist. As this is a case–control study, the reference standard will predate the index test. Variability in the reference standard will be examined using clinical photographs.

We have designed the study to include same day recruitment directly from clinic, therefore, the time between the reference standard and index test for most participants will be short. All participants receive the same reference standard (a dermatologist’s diagnosis), therefore, complete verification will be achieved. All participants will be included within the analysis and a complete data set sensitivity analysis is planned. Data are extracted from the medical record by an investigator who did not undertake the diagnostic criteria assessment (blinded to the index test).

### Patient and public involvement

The patient and public involvement aim in this study was to inform our understanding of the importance of diagnosis to patients, to make sure the study design was patient centred, to ensure the participant facing documents were what patients wanted and to inform dissemination. A patient advisor (CH) has been involved from the beginning of the project and is a study coauthor. PAPAA, a UK patient association, is a supporting organisation. We have also met the Young Person’s Advisory Group (YPAG) for Research Nottingham and patients in paediatric dermatology clinics.

The research questions were developed and informed by the patient association prioritisation work, discussion with our patient advisor and the YPAG. We discussed what diagnosis means to young people and the importance of being able to give a name to a disease. Important suggestions from these groups that have informed the study are presented in box 3. The above groups will guide dissemination to patient communities.

Box 3Suggestions from patient and public involvement work that have informed the DIPSOC studyStudy design.Include on the day recruitment and the option to attend for a separate research visit.Invite participants by letter in advance of their clinic appointment.Participant information sheetsChange the format to a leaflet or booklet.Colourful boxes around the text and different colours for different sections.Emphasise confidentiality and the assessment will take place in a private space.Include photographs of the research team.Do not include photographs of psoriasis.Provide electronic versions of the information sheets on a website.Create a distinctive logo for the studyProvide a colouring-in sheet.Give a certificate and sticker at the end of the research visit.

### Substudy

The objective of the substudy is to assess the performance of the best predictive diagnostic criteria to identify psoriasis in children/young people currently diagnosed with indeterminate disease. Children and young people with possible or indeterminate psoriasis will be recruited alongside the main study to the nested substudy. The eligibility criteria and research visit are otherwise identical to the main study. No control participant is required. Children/young people in the substudy will, if consent is provided, be sent a questionnaire 2 years after the last participant is recruited. The questionnaire will ask about their skin disease and whether the diagnosis has changed. The substudy data will be used to calculate the sensitivity and specificity of the best predictive criteria in identifying children and young people previously diagnosed with indeterminate psoriasis who go on to be diagnosed with psoriasis.

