**Methods and analysis:**

Children and young people (<18 years) with psoriasis (cases) and other scaly inflammatory skin diseases (controls) diagnosed by a dermatologist are eligible for recruitment. All participants complete a single research visit including a diagnostic criteria assessment by a trained investigator blinded to the participant’s diagnosis. The reference standard of a dermatologist’s diagnosis is extracted from the medical record. Sensitivity and specificity of the consensus derived diagnostic criteria will be calculated and the best predictive criteria developed using multivariate logistic regression.

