### Reference test

A dermatologist’s diagnosis as recorded in the participant’s medical record. The diagnosis is a clinical diagnosis and may include, but does not require, a skin biopsy.

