### Study progress

Twelve UK centres are open for recruitment. These centres are Nottingham, Barts London, Middlesbrough, Cambridge, Sheffield, Coventry, Glasgow, Dorchester, Oxford, St George’s London, Plymouth and Cardiff. The first participant was recruited in October 2017 and the study is due to finish recruiting on August 2019. We are currently in the data collection phase.

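### The substudy outcome is read at one calendar date, so follow-up from each child's own assessment varies from 24 to at most about 46 months and the pooled accuracy table has no common horizon

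*Protocol article*

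**What the plan says.** The Substudy section states that "Children and young people with possible or indeterminate psoriasis will be recruited alongside the main study to the nested substudy". Children who consent will "be sent a questionnaire 2 years after the last participant is recruited", and "The questionnaire will ask about their skin disease and whether the diagnosis has changed". The replies are then used to estimate how well the best predictive criteria identify "children and young people previously diagnosed with indeterminate psoriasis who go on to be diagnosed with psoriasis". That phrase carries no time limit.

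The criteria are assessed once. The Abstract says "All participants complete a single research visit including a diagnostic criteria assessment by a trained investigator blinded to the participant’s diagnosis", and the Substudy section makes the substudy visit the same as in the main study. Each child's follow-up clock therefore starts at that child's own visit.

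Under Study progress: "The first participant was recruited in October 2017 and the study is due to finish recruiting on August 2019".

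For the main study, the Reference test section takes the dermatologist's "diagnosis as recorded in the participant’s medical record".

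**The concern.** In the main study the diagnosis predates the assessment, so elapsed time plays no part in who is a case. In the substudy the outcome lies in the future, and the time allowed for it is part of what makes a child reference-positive. Here that time is set by the end of recruitment and not by the child's own visit.

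Two children with the same criteria result and the same disease course can then fall in different cells of the table because one was recruited earlier. The pooled sensitivity and specificity would refer to an unspecified mixture of horizons. A study with a different recruitment pace could not reproduce that mixture, and any extension of recruitment would widen it. The article fixes this timing rule itself, so the point is not a detail left to the analysis plan.

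**Working it through.** There is no sample size or power figure for the substudy to reproduce. The check is date arithmetic, followed by an illustration on assumed rates.

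**Inputs from the article**
- Start of recruitment: October 2017 (Study progress).
- Planned end of recruitment: August 2019 (Study progress).
- Questionnaire: last recruitment + 2 years (Substudy), so about August 2021.
- Start of each child's follow-up: the single research visit (Abstract; Substudy).

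**Follow-up range**
- Recruitment period: October 2017 to August 2019 = 22 months (21 to 23, depending on the days of the month).
- Last recruit: 24 months.
- Earliest possible recruit: 24 + 22 = 46 months, or 46/12 = 3.83 years (3.75 to 3.92 by day of the month).

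The 46 months is an upper bound. The article does not say when the first substudy child was recruited. If the last participant means the last in the main study, 24 months is a lower bound for the substudy. Either way there is one mailing date for all.

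**One child, two classifications**
- Suppose the diagnosis changes 30 months after the visit.
- August 2021 minus 30 months = February 2019.
- Recruited by about February 2019: the change precedes the mailing, so the child is reference-positive.
- Recruited from about March to August 2019: the change follows the mailing, so the same child is reference-negative.

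**Illustration only (no conversion rate is given in the article)**

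With a constant yearly rate r, the share converted by time t is 1 − exp(−r·t).

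| Assumed r | 24 months | 46 months | Ratio |
|---|---|---|---|
| 0.10 | 1 − exp(−0.200) = 0.181 | 1 − exp(−0.383) = 0.318 | 1.8 |
| 0.20 | 1 − exp(−0.400) = 0.330 | 1 − exp(−0.767) = 0.535 | 1.6 |

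If every change of diagnosis occurred within 24 months, the ratio would be 1.0.

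For accuracy, assume further that half the children are criteria-positive. Let a and b be the shares converted among criteria-positive and criteria-negative children. Then sensitivity = a/(a + b) and specificity = (1 − b)/[(1 − b) + (1 − a)].

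| Assumed 2-year conversion (positive vs negative) | Sensitivity / specificity at 2 years | Sensitivity / specificity at 3.83 years |
|---|---|---|
| 50% vs 20% | 0.71 / 0.62 | 0.68 / 0.71 |
| 60% vs 10% | 0.86 / 0.69 | 0.82 / 0.83 |

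For the 60% vs 10% row at 2 years: 0.6/(0.6 + 0.1) = 0.86 and 0.9/(0.9 + 0.4) = 0.69. Under the constant rate, a = 0.827 and b = 0.183 at 3.83 years, so 0.827/1.010 = 0.82 and 0.817/(0.817 + 0.173) = 0.83.

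These columns compare the two extremes. A pooled table would lie between them.

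**The case against.** The strongest objection is that the timing may be deliberate. The Substudy objective and the opening of the Discussion can be read as saying that psoriasis is already present at an indeterminate stage and that follow-up merely verifies it. On that reading two years is a guaranteed minimum and longer follow-up verifies better. A strict 24-month cut-off would then count a child with psoriasis confirmed at month 30 as negative. This stands, and it rules out replacing the all-follow-up result with a 24-month one. It does not remove the problem, because late recruits still get less verification time than early ones.

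A reader might infer from the illustration that the estimates are distorted by a known amount or in a known direction. The documents do not support that. The conversion rates, the constant hazard and the share of criteria-positive children are all assumed. If most diagnoses settle within two years the effect is small, and nothing suggests that recruitment date is related to the criteria result.

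A reader might also infer that the outcome rests on an unconfirmed family label and is therefore less accurate than the main reference standard. The article goes only part of the way. It mentions a questionnaire and no check against the record, but a family may be relaying a dermatologist's diagnosis. The questionnaire itself is not shown and may already ask for the date and source of the diagnosis.

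**Conclusion.** The concern holds in a limited form. The stated mailing rule gives follow-up of 24 months to at most about 46 months from the child's own assessment, and the target of a later psoriasis diagnosis has no stated horizon. One pooled table therefore depends in part on the recruitment calendar. The range rests on the planned recruitment dates and on substudy recruitment starting near October 2017; a later start narrows it but does not give a common horizon unless all the children were recruited together.

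The size of the effect on sensitivity and specificity cannot be determined from the article. The point concerns the nested substudy alone and leaves the primary and secondary objectives untouched. It should be settled before the questionnaire goes out.

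**What to change.** - Keep the single mailing, or mail at 24 months from each child's visit. If mailing is moved to 24 months, a later contact or record check is needed to pick up later diagnoses.
- Ask for the month and year of any changed diagnosis and who made it, if the questionnaire does not already do so.
- Report sensitivity and specificity at 24 months from each child's research visit. Under the current mailing rule every child reaches that point, so none is lost from this table through short follow-up.
- Report beside it the result using all available follow-up, with the range of follow-up stated, so that later confirmed diagnoses are kept.
- Where consent allows, confirm the diagnosis and its date from the medical record, in line with the main study.

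The cost is one or two questionnaire items, some recall error in the dates, and two tables instead of one.

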## Ethics and dissemination

### Ethics

The four principles of biomedical ethics were considered in the study design and documentation. The purpose, aims and details of taking part in the study are explained in the participant information sheets. It is explained that taking part is voluntary and not taking part will have no effect on the patient’s medical care. Informed consent is necessary before any part of the study is completed. It is also explained that taking part in the study will have no direct medical benefit for the patient, but may help the diagnosis of other children or young people in the future. The study is non-interventional and non-therapeutic. All study investigators are required to be Good Clinical Practice trained.

### Dissemination

Dissemination will be guided by stakeholders; patients, children and young people, dermatologists, primary care and paediatric rheumatologists. The aim is to publish the study results in a high-quality peer-reviewed journal and present the findings at international academic meetings. The results will also be shared through social media and the supporting patient association (PAPAA).

## Discussion

DIPSOC is a development study and the first in a series of studies needed to develop, test and validate the diagnostic accuracy of criteria for psoriasis in children/young people. The nested substudy will be important to investigate whether the criteria can help identify children with psoriasis at an indeterminate stage, before their skin disease may have fully evolved.

The development and introduction of diagnostic criteria for psoriasis in children/young people has the potential to improve the early and accurate recognition of psoriasis and juvenile psoriatic arthritis, prompt referral for specialist assessment and monitoring, standardise clinical research to enable meta-analysis of data and support case finding in new epidemiological studies. The utility of diagnostic criteria will, therefore, be in primary and secondary care as well as clinical research.

### Limitations

DIPSOC has been designed to ensure a high-quality diagnostic study, but there are some important limitations. A case–control study design is likely to overestimate the diagnostic accuracy of the criteria. DIPSOC is a development study, and therefore, this study design is appropriate and feasible for this early stage of testing. In the future, further diagnostic cohort studies are needed to test, potentially improve, and validate the resulting criteria in the setting and population they are intended to be used. Another limitation of the study design is spectrum bias. Participants recruited from paediatric dermatology clinics are likely to have more severe and persistent disease (ie, a different clinical presentation) compared with children/young people in the community who are managed by general practitioners. This spectrum bias may lead to an overestimation of the diagnostic accuracy because participants may have more obvious disease. DIPSOC recruits both new and follow-up (incident and prevalent) patients. This will include participants currently on treatment who’s skin rashes may have changed since starting treatment. However, paediatric dermatology clinics are a feasible setting to recruit the required sample size and obtain a reference standard to ensure complete verification. DIPSOC does not include external validation of the best predictive criteria and this will need to be undertaken in separate studies once the diagnostic criteria have been developed.

### Study progress

Twelve UK centres are open for recruitment. These centres are Nottingham, Barts London, Middlesbrough, Cambridge, Sheffield, Coventry, Glasgow, Dorchester, Oxford, St George’s London, Plymouth and Cardiff. The first participant was recruited in October 2017 and the study is due to finish recruiting on August 2019. We are currently in the data collection phase.
